### Secondary objectives

To assess intervention and control efficacy in selected health facilities, in order to compare: 1) Time to start positive pressure ventilation after birth; 2) Time to achieve heart rate greater or equal than 100 per minute; 3) Apgar at 1 minute and at 5 minutes; 4) Use of supplemental oxygen after 10 minutes of life; 5) Inspiratory oxygen fraction needed at 30 minutes after birth; 6) Mortality rate during the first 7 days of life; 7) Number of referrals to health facilities with greater resolution capacity during the first 7 days of life; 8) Number of certified health professionals as providers.; and 9) Number of certified health professionals as instructors.

The efficacy of the evaluation will be evaluated at 6 months after the intervention.

Status of the study: This study is ongoing.

Study protocol version 1.0 – March 31th, 2017.

Trial registration data can be found in
Supplementary File 1.

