### Standard training

Standard training will be conducted through a theoretical-practical course, which will be administered once during the study period, to all health professionals of the selected facilities, according to the randomization. It is an 8-hour course, with 3 hours of theory (based on suggested readings) and 5 hours of practice, which will take place during a single day, from 9:00 a.m. to 6:00 p.m. The course will be performed by staff of the Neonatal Unit of the National Institute of Child Health, and will be coordinated by an NRP instructor accredited by the American Academy of Pediatrics. Suggested readings will include the following sequential topics: 1) Initial Steps, 2) Positive Pressure Ventilation, 3) Cardiac Massage, 4) Intubation and Medications, and 5) General Review. Practical sessions will be carried out in groups, with 10 or more people per group, and will include all the health professionals of the facility. The practical content part will consist of simulations based on predetermined scenarios using neonatal mannequins and supplies needed for basic and advanced resuscitation, covering each component of the theoretical content. One instructor will be assigned to each group. A baseline and a follow-up theoretical test will be administered.

Participants completing their attendance to theoretical sessions, participating in the simulated practices and approving the printed exams taken the same day will we granted a Standard Certification. The practice will be evaluated qualitatively in terms of assistance, participation and performance of activities.

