^22^. The learning is completed according to the student’s pace and needs, and the platforms offer didactic material. The learning process can be done in groups, but the exam is online and individual, and requires Internet connection. Staff can be trained to become a provider and then qualify to become an instructor. At least one instructor will be certified at each facility in order to train the trainers for continuing education in every facility. Instructors will be given access to the web platform to include news of their activities and to evaluate the practices of aspiring providers in their health facilities. 

The theoretical online exam consists of 40 questions distributed in four modules encompassing basic and advanced neonatal resuscitation. Basic modules include a) Initial Steps of Resuscitation, and b) Positive Pressure Ventilation. Advanced modules include c) External cardiac massage, and d) Intubation and Medications.

Examination for each module allows unlimited attempts, and it is necessary to achieve at least 60% success to be approved. According to approved modules and practices, health personnel can obtain a supplier or instructor certification in both basic neonatal resuscitation and advanced neonatal resuscitation. Two types of examination have been prepared, according to the objective of the applicant. One is an aimed at applicants to Neonatal Resuscitation Provider. The other one, an advanced exam, is for applicants to Neonatal Resuscitation Instructor.

All participants need to complete both the Theoretical and the Practical training components. The platform also will allow the use of an agenda-type tool for scheduling practices for aspiring providers or instructors who have passed their online exam. The Theoretical Component is available after the candidate has been registered in the multi-platform portal, to which they can access through a PC, tablet or cell phone with Internet connection. Access to the content is online the first time, but it may also be offline, after downloading the corresponding training modules.

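### The certified-instructor count cannot serve as a between-arm efficacy outcome, because only MP-ICT is described as certifying instructors; the certified-provider count compares unlike certificates

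*Protocol article*

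**What the plan says.** The protocol article's Secondary objectives introduce nine outcomes as a comparison of efficacy between intervention and control. The eighth is "Number of certified health professionals as providers" and the ninth is "Number of certified health professionals as instructors". Statistical analysis assigns secondary outcomes a t-test or a Kruskal-Wallis test and makes no exception for these two.

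The certification rules differ by arm:

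- **Multi-platform ICT training.** There are two tiers: "health personnel can obtain a supplier or instructor certification in both basic neonatal resuscitation and advanced neonatal resuscitation". Instructor applicants have their own advanced exam. The section also sets a target: "At least one instructor will be certified at each facility in order to train the trainers for continuing education in every facility". On the theory exam: "Examination for each module allows unlimited attempts, and it is necessary to achieve at least 60% success to be approved". The exam needs an Internet connection. Candidates who pass must then book a practical session with an instructor and pass a practical assessment.
- **Standard training.** The course is to be "administered once during the study period, to all health professionals of the selected facilities" and lasts one day. Those who attend, take part in the simulations and finish by "approving the printed exams taken the same day will we granted a Standard Certification". Practice is judged qualitatively. No instructor tier, pass mark or resit rule is described, and the text does not say whether this certificate counts as a provider certificate.

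**The concern.** An efficacy outcome should be able to come out either way, depending on whether the intervention works. As described, the instructor count cannot: producing instructors is a component of MP-ICT and no part of the control course. A test of it asks whether the intervention was carried out.

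The provider count has a milder problem. Both arms can certify staff, but against different hurdles, so a difference in either direction mixes uptake, exam rules and training effect. It is also a raw count, and Randomization matches facilities on the proportion of non-medical professionals and on equipment, not on the number of staff.

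What is at stake is interpretation. Expected results foresees national scale-up of this certification strategy if it proves effective. A small p-value for instructors, listed beside clinical outcomes under efficacy, could be taken as support for that decision when it carries no information on skill or newborn outcome.

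**Working it through.** The protocol gives no expected figure for either certification outcome, so there is none to reproduce.

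**Instructors (outcome 9)**

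Inputs: six facilities per arm (Sample size); at least one instructor per MP-ICT facility (Multi-platform ICT training); none per control facility (no route described in Standard training); alpha 5% (Sample size; two-sided assumed). The least extreme pattern that meets the plan is 1,1,1,1,1,1 against 0,0,0,0,0,0.

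1. *Kruskal-Wallis.* Mid-ranks are 3.5 for each zero and 9.5 for each one, so the rank sums are 21 and 57.
   - Uncorrected H = 12/(12×13) × (21²/6 + 57²/6) − 3×13 = 8.31.
   - Tie correction = 1 − 2(6³ − 6)/(12³ − 12) = 1 − 420/1716 = 0.755.
   - H = 8.31/0.755 = 11.0 on 1 df, asymptotic p = 0.0009.
2. *Exact test on facilities.* There are C(12,6) = 924 allocations, and two are as extreme as this one: p = 2/924 = 0.0022.
3. *Matched pairs.* Randomization pairs facilities before allocating them. With six pairs all in the same direction, the sign-flip p = 2 × 0.5⁶ = 2/64 = 0.031.

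The t-test, the other named option, is degenerate here because neither arm has any variance. With an illustrative uneven pattern (1, 1, 2, 1, 3, 2 against six zeros), the t-test gives p = 0.0005 and Kruskal-Wallis p = 0.0019.

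All these p-values are below 0.05, and no quantity describing skill entered the calculation.

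**Providers (outcome 8)**

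The rates below are assumptions, because the protocol gives none.

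*Repeat attempts.* Suppose all four modules are required, attempts are independent and the chance of passing a module at one attempt is p. The chance of passing all four within k attempts each is (1 − (1 − p)^k)⁴. At p = 0.7 this is 0.24 for k = 1, 0.90 for k = 3 and 0.99 for k = 5. Taken alone, unlimited attempts favour MP-ICT.

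*Uptake.* Certified share = uptake × pass. MP-ICT staff must work through the material, sit an online exam, book a practical and pass it; control staff all receive one course on one day.

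| Control (uptake × pass) | MP-ICT (uptake × pass) | MP-ICT minus control |
|---|---|---|
| 0.95 × 0.90 = 0.855 | 0.90 × 0.95 = 0.855 | 0 |
| 0.95 × 0.90 = 0.855 | 0.50 × 0.90 = 0.45 | −0.405 |
| 0.60 × 0.60 = 0.36 | 0.90 × 0.95 = 0.855 | +0.495 |

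The sign is open.

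*Raw counts.* If 80% of staff are certified in two facilities (assumed), one with 10 staff contributes 8 and one with 50 contributes 40. The counts differ fivefold although the rates are equal.

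**The case against.** The strongest reply is that certification is what the programme delivers. The article gives erratic frequency and low uptake of conventional courses as part of the problem, so numbers certified are a sensible programme outcome, and the primary hypothesis rests on heart rate, not on certificates. This stands. It is a reason to keep both measures, as uptake and implementation, but not to test the instructor count as efficacy.

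Second, zero instructors in the control arm is an inference: Standard training describes no instructor tier but does not forbid one, and an article condenses a fuller protocol. This stands as a caveat, and the p-values depend on it. The target sentence sits under the MP-ICT heading, and the next sentence gives instructors access to the web platform. If "At least one instructor will be certified at each facility in order to train the trainers" was meant for both arms, the Standard training section does not provide for it and the two sections must be reconciled.

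Third, Description of interventions says that theoretical and clinical skills will be formally assessed by exams taken by participants in each group, so competence is not judged from certificate counts alone. That is fair. But the exams then described differ between the arms, so they supply no common yardstick.

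A reader might go further and infer that both certification outcomes are decided in advance and that unlimited attempts guarantee an MP-ICT advantage in providers too. The documents do not support this. Both arms can certify staff, and the Internet exam, the booking step and the assessed practical work against MP-ICT, while the control course reaches all staff in a day. Nor does the article say that it would present these counts as proof of better resuscitation.

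**Conclusion.** The concern holds in full for the instructor count and in a limited form for the provider count.

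- **Instructors.** If at least one instructor is certified in each of six MP-ICT facilities and none in six control facilities, the between-arm test is significant by construction (p between 0.0009 and 0.031, depending on the test). The matched-pair value of 0.031 fits the design best; 0.0009 is an asymptotic value that ignores the pairing. The conclusion assumes delivery as described and no undisclosed control route.
- **Providers.** The result is not predetermined. The defect is that the certificates have different criteria and the counts have no denominator, so neither a positive nor a negative difference can be read as efficacy.

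These are two of nine secondary outcomes. The primary comparison and its conclusion are untouched. The change should be made, but the trial does not depend on it.

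**What to change.** 1. Remove the number of certified instructors from the between-arm efficacy tests. Report it descriptively, per facility, as an implementation measure in the MP-ICT arm.
2. Report certified providers as the percentage of eligible delivery-attending staff in each facility who are certified. Label it uptake or process, not efficacy or competence, and state whether a Standard Certification counts as a provider certificate.
3. If the arms are to be compared on competence, use one criterion applied identically in both: same test, pass mark, attempt rule and timing. Its items should not come from the MP-ICT online exam, because MP-ICT staff may have met those questions repeatedly and control staff would see them for the first time.

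Items 1 and 2 cost a change of wording and a staff list per facility for the denominator. Item 3 is optional and would need new test items and a sitting in each arm. The downside is that one or two secondary outcomes no longer count as efficacy evidence.

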## Research methodology and experimental plan

### Settings

Ayacucho and Cusco are two Peruvian regions located to the south of the country. Both regions were selected as thay have a neonatal mortality rate above 15 per 1,000 live births and they are accessible through air travel. These regions cover areas of Andean highlands, but their territory is mainly on the Amazon rainforest (Peru Export and Tourism Promotion Board, 2017;
http://www.peru.travel). Also, in those departments there is the “Valley of the Apurímac, Ene and Mantaro Rivers”, also known as the VRAEM, which is extremely poor and one of the major areas of coca growing in Peru
^19^.

According to the Peruvian Registry of Institutions that Provide Health Services (RENIPRESS), Ayacucho has 418 and Cusco 848 registered health facilities (
*Registro Nacional de Instituciones Prestadoras de Servicios de Salud 2017* website;
http://www.minsa.gob.pe/portalweb/02estadistica/estadistica_2.asp?sub5=2). However, last year (2016) almost 15,000 deliveries were attended at 80 public health facilities of primary and secondary level, which represents 50% of all deliveries in both regions (
*Sistema de Registro del Certificado de Nacido Vivo en Linea* 2017 website;
http://www.minsa.gob.pe/cnv/).

Basic teams are composed by doctors, nurses, midwives and nurse technicians, who are registered in a database updated by the health personnel observatory reports (
*Observatorio de recursos humanos en salud* 2017 website;
http://observatorio.inforhus.gob.pe/). This observatory states that, up until June 11
^th^, 2017, Ayacucho had 337 doctors, 726 nurses, 466 midwives and 743 nurse technicians; while Cusco had 661 doctors, 942 nurses, 486 midwives and 806 nurse technicians.

### Study design

The proposed study design is a randomized cluster trial. The units of study and analysis will be twelve health facilities from Ayacucho and Cusco departments. Each health facility will be a cluster. Clusters will be randomly assigned either to the MP-ICT course and certification package (intervention) or to the standard training and certification package (control). Additional details are shown in
Table 1.

**Table 1. T1:** Schedule of enrolment, interventions, assessments and final report: RCPNEOPERU Project.

	STUDY PERIOD									
	Project Management		Allocation	Post-allocation		Pause	Assessments			Close-out
BIMESTER	*B _-2_*	*B _-1_*	*0*	*B _3_*	*B _4_*	*B _5_*	*B _6_*	*B _7_*	*B _8_*	*B _9_*
	*2017-04* *2017-05*	*2017-06* *2017-07*		*2017-08* *2017-09*	*2017-10* *2017-11*	*2017-12* *2018-01*	*2018-02* *2018-03*	*2018-04* *2018-05*	*2018-06* *2018-07*	*2018-08* *2018-09*
**ENROLMENT**										
Ethical approval and Logistics	**X**	**X**								
Allocation			**X**							
Eligibility screen				**X**						
Informed consent				**X**						
**INTERVENTIONS**										
Intervention ICT										
Standard control										
**ASSESSMENTS**										
Baseline				**X**						
Primary Outcome							**X**	**X**	**X**	**X**
Other Outcomes							**X**	**X**	**X**	**X**
**FINAL REPORT**										**X**

**Legend**: Intervention ICT=Training and certification using Information and Communications Technology
**Template reference**: Chan A-W, Tetzlaff JM, Gøtzsche PC, Altman DG, Mann H, Berlin JA,
*et al.* SPIRIT 2013 explanation and elaboration: guidance for protocols of clinical trials. BMJ: British Medical Journal. 2013;346.

### Justification for design

The primary target of the intervention is the health provider. However, we made the decision to assess the heart rate of infants as an objective and practical way to evaluate the effect of the intervention on the adequacy of the resuscitation provided by the health worker, in line with other studies targeted primarily to the health provider
^20^. Training will be provided to groups of health professionals who work at a health facility. Also, because of the geographical distribution of health facilities, their selection as units of study helps to minimize the possibility of contamination between interventions.

### Inclusion and exclusion criteria

Primary and secondary level facilities located in Ayacucho and Cusco that have a neonatal mortality rate higher than 15 per 1,000 livebirths will be eligible. Health facilities whose authorities refuse participation of their health professionals, facilities with less than 290 births a year, facilities located at more than 210 kilometers from the department capital, and those located in high-risk areas due to social unrest will be excluded. Health professionals who attend deliveries and accept their voluntary participation will be included after signing informed consent forms.

### Sample size

We must emphasize that our study will be conducted at a pilot scale and thus we considered the minimum sample size for such study level. Assuming the occurrence of about 4,000 births during a period of 6 months of filed study observation, we aim at discriminating a 4% difference in the proportion of newborns with heart rate equal or greater than 100 beats per minute at two minutes of life between the intervention and the control group
^18^. We would require 12 clusters (health facilities) divided in two arms, with six facilities allocated to each arm, and with an average of 334 deliveries per facility during the observation period. The proposed power of the study is 80% and the acceptable alpha error is 5%. The percentage for heart rate >100 bpm at two minutes of life during suitable resuscitation using self-inflated bag is 90%
^21^, and it is the expected value for the intervention group. For the control group, at least 4 percentage points below the value achieved in the intervention group is expected (i.e. no more than 86%).

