## Introduction

### Background

Approximately 10% of newborns may have difficulty breathing at birth and require urgent support from trained personnel
^1^. The first 60 seconds of life in those conditions require immediate and effective interventions to help infants survive
^2^. Unfortunately, some newborns in low- and middle-income countries do not have access to appropriately trained personnel, making asphyxia one of the leading causes of neonatal death in those settings
^3^.

In Peru, about 550,000 births occur per year (Peruvian Institute for Statistics and Informatics 2015;
https://www.inei.gob.pe), and this means that approximately 6 newborns each hour may require respiratory support at birth. Problems in training health workers for adequate support of newborns is aggravated by a high turnover rate of personnel, particularly in small cities and rural areas, which hampers regular conduction of local training programs, even if they are perceived as a positive incentive
^4^. Peru is a high-middle-income country that has made significant progress in reducing neonatal and infant mortality in the last decade, despite inequities in access to health services, especially in rural areas of the Amazon and the Andes
^5,
6^. In the years 2011–2012, the Peruvian neonatal mortality rate was estimated at 12.8 per thousand live births
^7^, with an estimated 20 per thousand live births for Pasco and Cusco regions, 15 for Ayacucho and Amazonas, 12 for Huancavelica and 8 for Lima
^8^. From 2000 to 2013, neonatal mortality in Peru fell by 51% from 16.2 deaths per 1000 livebirths to 8.0
^9^.

The Neonatal Resuscitation Program (NRP) from the American Academy of Pediatrics, includes evidence-based clinical guidelines and was designed to train health care providers and instructors in hospital settings. The NRP is a paid course that has 2 components, an online component (internet-dependent) and a practice/evaluation component
^1,
10^. A variant of the NRP program is the Helping Babies Breath (HBB) program, which was designed to provide neonatal resuscitation training in resource-poor settings. The HBB has shown to reduce neonatal mortality and it is proposed as a successful global intervention
^11^. However, the greatest limitation of these programs is the need for recurrent training with a frequency of less than 12 months to maintain the acquired skills and knowledge
^12^.

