### Outcomes

Our primary outcome is the percentage of infants with heart rate equal or greater than 100 per minute at two minutes of life. This outcome is an adequate proxy for effective response to neonatal resuscitation measures in the delivery room
^20,
21,
23^.

The secondary outcomes are described in our secondary objectives.

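### The 90% and 86% planning rates come from bag resuscitation but are applied to all 4,000 births, so the stated 80% power is not supported

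*Protocol article*

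**What the plan says.** All the planning figures are in the Sample size section of the protocol article.

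- **Intervention rate:** "The percentage for heart rate >100 bpm at two minutes of life during suitable resuscitation using self-inflated bag is 90" (per cent), "and it is the expected value for the intervention group".
- **Control rate:** "For the control group, at least 4 percentage points below the value achieved in the intervention group is expected (i.e. no more than 86" (per cent). No separate source is given.
- **Target:** "we aim at discriminating a 4% difference in the proportion of newborns with heart rate equal or greater than 100 beats per minute".
- **Number observed:** "Assuming the occurrence of about 4,000 births during a period of 6 months of filed study observation", in 12 facilities, six per arm, averaging 334 deliveries each.
- **Error rates:** 80% power and 5% alpha. Sidedness, intracluster correlation (ICC) and design effect are not given.

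The Outcomes section reads: "Our primary outcome is the percentage of infants with heart rate equal or greater than 100 per minute at two minutes of life". It does not restrict this to resuscitated newborns, though it presents the measure as a proxy for response to resuscitation. The Background states: "Approximately 10% of newborns may have difficulty breathing at birth and require urgent support from trained personnel".

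**The concern.** The rate and the count belong to different populations. The 90% describes newborns receiving bag ventilation, while the 4,000 counts every delivery. Nothing in the section converts a resuscitated-newborn rate into an all-births rate, or 4,000 births into the roughly 400 newborns who would need support at the protocol's own 10%.

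Under the first reading the sample is about a tenth of what was counted. Under the second, an effect confined to one birth in ten is diluted about tenfold. If the power is really nearer 20% than 80%, a trial of a training programme with the assumed benefit would more often than not end without a significant result, and a reader who trusts the 80% would give that result too much weight.

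**Working it through.** **Inputs.** From Sample size: 90%, 86%, 12 facilities × 334 = 4,008 births, 2,004 per arm, alpha 5%, power 80%. From Background: 10% need support. Assumed here: a two-sided test, and no clustering unless stated.

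**Formulas.** With d = p1 − p2 and p̄ = (p1 + p2)/2:

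- n per arm = [1.96·√(2p̄(1−p̄)) + 0.842·√(p1(1−p1) + p2(1−p2))]² / d²
- power = Φ{(d − 1.96·√(2p̄(1−p̄)/n)) / √((p1(1−p1) + p2(1−p2))/n)}
- all-births rate = s·p + (1 − s)·q, where s is the share resuscitated, p the rate among them and q the rate in the other infants.

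**1. The plan's own figure, taken literally over all births.** For 90% vs 86%, n = 1,035 per arm, against 2,004 planned. At 2,004 per arm the power is Φ{(0.04 − 1.96 × 0.01027)/0.01025} = Φ(1.94) = 97.4%. The stated 80% appears only with an unstated design effect of 2,004/1,035 = 1.94, that is, an ICC of (1.94 − 1)/333 ≈ 0.0028. A t-test on 10 degrees of freedom at that ICC gives 72%.

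**2. Do those rates fit the 10% figure?**

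- 86% over all births puts 14% of infants below 100 beats per minute at two minutes, which is more than the 10% said to need any support.
- 90% over all births puts 10% below, which equals the whole group needing support, and this in the arm expected to do well.
- A 4-point gap over all births that arises only in that 10% needs a gap of 0.04/0.10 = 40 points among them.

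**3. Denominator: resuscitated newborns.** n = 0.10 × 2,004 ≈ 200 per arm. Power for 90% vs 86% is Φ{(0.04 − 1.96 × 0.03246)/0.03240} = Φ(−0.73) = 23%.

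| Share resuscitated | n per arm | Power |
|---|---|---|
| 5% | 100 | 14% |
| 10% | 200 | 23% |
| 20% | 401 | 41% |

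For 80% power, 1,035/2,004 ≈ 52% of births would have to be resuscitated.

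**4. Denominator: all births.** Assume s = 10%, q = 100% in both arms, and no training effect in the other infants.

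- Intervention: 0.1 × 0.90 + 0.9 × 1 = 99.0%
- Control: 0.1 × 0.86 + 0.9 × 1 = 98.6%
- Power: Φ{(0.004 − 1.96 × 0.003440)/0.003439} = Φ(−0.80) = 21%
- n for 80% power: about 11,630 per arm

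| s | q | Rates | Power |
|---|---|---|---|
| 5% | 100% | 99.5% vs 99.3% | 13% |
| 10% | 100% | 99.0% vs 98.6% | 21% |
| 10% | 99% | 98.1% vs 97.7% | 14% |
| 20% | 100% | 98.0% vs 97.2% | 38% |

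**5. Relaxing the no-effect assumption.** Suppose the other infants are at 99.5% vs 98.5%, with 90% vs 86% in the rest. The rates become 0.09 + 0.8955 = 98.55% and 0.086 + 0.8865 = 97.25%, and the power is 82%.

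**6. Clustering.** Any positive ICC lowers every figure in steps 3 to 5. At 0.0028, the 23% becomes 19–22% and the 21% becomes 12–13%, depending on whether the t or the normal approximation is used.

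**The case against.** The strongest reply is that the plan's figures are workable if taken at face value. With 90% and 86% over about 2,004 births per arm, power is 97% before clustering, and 80% is reached at a small ICC. A reader might infer that the section contains a calculation error, or that 80% power is impossible under either denominator. The document supports neither. No calculation in it is shown to be wrong, and power falls only once the rates are tied to the population they came from. What fails is the use of 90% as an all-births rate, which the text ties to bag resuscitation and the 10% figure contradicts.

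The all-births result of 21% also needs a rate in non-resuscitated infants that the document does not give, and no training effect in them. Both courses teach initial steps, which are not confined to ventilated infants. A 1-point benefit in the others would bring power to 82% (step 5). Nothing in the document makes such a benefit likely, but nothing excludes it. This point stands, so 99.0% and 98.6% are illustrations and not rates to adopt.

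Three further points carry some weight:

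- The 10% is a general figure and these facilities were chosen for high neonatal mortality. Across 5% to 20%, however, power stays between 13% and 41% under the assumptions of steps 3 and 4.
- Four points is worded as a minimum, and 90% vs 80% in 200 newborns per arm would give 80% power before clustering. The power claim, however, is made for 4 points.
- The study calls itself pilot scale. That tempers the consequence but does not justify stating 80%.

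It might also be inferred that all births must be the denominator because the outcome is worded for infants. The protocol also presents the outcome as a measure of response to resuscitation, so either population may be intended.

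**Conclusion.** The concern holds in this form: a rate from resuscitated newborns, and a control rate derived from it by subtraction, are applied to all deliveries, so 80% power for a 4-point difference is not supported.

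The firmer figure is for resuscitated newborns: about 23% before clustering (14% to 41% for shares of 5% to 20%). It needs only the protocol's own rates and a share needing resuscitation. The all-births figure, about 21% (13% to 38% over the same shares; 14% if 99% of the others reach 100 beats per minute), is conditional on the rate in the other infants and on training having no effect in them. A training effect there would raise it. Clustering lowers all of these figures.

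**What to change.** In Outcomes, state one denominator for the primary outcome: all births or resuscitated newborns. In Sample size, restate the expected rate in each arm, the detectable difference and the power for that denominator, each with a source that matches it. If all births are chosen, state the rate and any training effect assumed in non-resuscitated infants, and show the power over a range of both. Withdraw the 80% claim unless the restated figures support it.

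The choice of denominator and the sourcing of the rates belong to the sponsor. The cost is a change of wording and, probably, a less favourable stated power. No extra enrolment is needed.
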